## Abstract

**Introduction:**

With the widespread use of electronic health records and handheld electronic devices in hospitals, informatics-based antimicrobial stewardship interventions hold great promise as tools to promote appropriate antimicrobial drug prescribing. However, more research is needed to evaluate their optimal design and impact on quantity and quality of antimicrobial prescribing.

**Methods and analysis:**

Use of smartphone-based digital stewardship applications (apps) with local guideline directed empirical antimicrobial use by physicians will be compared with antimicrobial prescription as per usual as primary outcome in three hospitals in the Netherlands, Sweden and Switzerland. Secondary outcomes will include antimicrobial use metrics, clinical and process outcomes. A multicentre stepped-wedge cluster randomised trial will randomise entities defined as wards or specialty regarding time of introduction of the intervention. We will include 36 hospital entities with seven measurement periods in which the primary outcome will be measured in 15 participating patients per time period per cluster. At participating wards, patients of at least 18 years of age using antimicrobials will be included. After a baseline period of 2-week measurements, six periods of 4 weeks will follow in which the intervention is introduced in 6 wards (in three hospitals) until all 36 wards have implemented the intervention. Thereafter, we allow use of the app by everyone, and evaluate the sustainability of the app use 6 months later.

**Ethics and dissemination:**

This protocol has been approved by the institutional review board of each participating centre. Results will be disseminated via media, to healthcare professionals via professional training and meetings and to researchers via conferences and publications.

**Trial registration number:**

ClinicalTrials.gov registry (NCT03793946). Stage; pre-results.

Strengths and limitations of this studyThis study will be an international randomised, multicentre, clinical trial using a rigorous design and methodology to evaluate the impact of an antimicrobial stewardship smartphone application (app) for the hospital setting.The app can easily be adapted to local guidelines which is a key feature for potential future use in other settings.The primary outcome is appropriate empiric antimicrobial therapy. The study is conducted in three hospitals with relatively high rates of appropriate antibiotic use, which may theoretically lead to a higher risk of a negative trial.In this cluster randomised trial, wards/specialties are the unit of randomisation and there is a risk of contamination through physicians changing between wards or among specialties, although this risk is lower than for a single-centre randomised trial. Restricted access to the software and tracking of app use will be applied to monitor possible contamination.

## Introduction

Antimicrobial drugs are an indispensable part of modern medicine, which depends on effective drugs for prophylaxis and treatment. Yet, only around 40%–70% of empiric antimicrobial regimens are considered appropriate with regard to their indication, the choice of agent, dosing or duration.^1–4^ Inappropriate antimicrobial use enhances the risks of treatment failure and side effects in the individual patient, and accelerates selection and transmission of antimicrobial-resistant pathogens in healthcare settings and the community.^5^ Many antimicrobial stewardship (AMS) interventions have been shown to increase appropriateness of antimicrobial drug prescribing.^6^

A software application (app), which is compatible with mobile electronic devices such as smartphones and tablets, and increases the availability of existing national and local antibiotic guidelines plus local antibiograms, may improve antimicrobial prescribing, reduce medication errors and ultimately improve patient outcome. Due to its highly customisable nature, a digital app has the potential to become an effective AMS tool in all countries.

Mobile-software apps seem particularly interesting for the purpose of AMS, since they do not require access to electronic health records (EHRs) or computerised physician order entry systems, that are costly, difficult to maintain and not easily customisable. Most healthcare workers own a smartphone and often use it to access information to assist in their treatment decisions.^7 8^ The vast majority of available apps developed to support prescription of medicines are limited to knowledge content and do not provide decision support algorithms. Further, they have rarely been evaluated in clinical trials.^9^ To date, most reported digital AMS interventions are single-centre studies with limited internal validity due to methodological limitations and uncertain external validity.^4 10 11^

In the present study, we will evaluate the implementation and impact of a smartphone-based software app (the AB-Assistant, Spectrum, Calgary, Canada) adapted to local conditions in an international clinical trial using a stepped-wedge cluster randomised design and appropriateness of empiric antimicrobial prescribing as the primary outcome.

## Methods and analysis

### Setting

This study will be conducted in three academic, tertiary care hospitals in Europe: Erasmus University Medical Center, Rotterdam, the Netherlands; Uppsala University Hospital, Uppsala, Sweden and Geneva University Hospitals, Geneva, Switzerland (table 1).

**Table 1 T1:** Characteristics of the participating centres

Name	Geneva University Hospitals	Erasmus MC Rotterdam	Uppsala University Hospital
Website	www.hug-ge.ch/en/	https://www.erasmusmc.nl/	https://www.akademiska.se/en/
Abbreviation	HUG	EMC	UUH
City	Geneva	Rotterdam	Uppsala
Country	Switzerland	The Netherlands	Sweden
Care level	Primary and tertiary care	Tertiary care	Tertiary care
Academic affiliation	Yes	Yes	Yes
Number of beds	About 1 900	900	About 1 000
Availability of antibiotic guidelines	Paper format and PDF	Website containing local guidelines. Updated every 2 years. Guidelines are based on the national guidelines of SWAB	Local guidelines in paper format and online (pdf). Updated every 2–3 years.
	Updated every 2 years		National guidelines provided by STRAMA available online and in app format, not routinely used at UUH.
	Integrated into the EHR in some units in the context of a different study (Trial registration number: NCT03120975); COMPASS units not participating in this study		
Current standard of care antimicrobial stewardship	On demand ID consultations	On demand ID consultations	On demand ID consultations
	Review of all positive blood cultures	Daily rounds on Intensive care units, weekly rounds on all units	Daily rounds on intensive care units
	Daily rounds on some units	Review and feedback for certain antibiotics	Adapted information and feedback to physicians at major departments 1–2 times per year
	Approval required for certain antibiotics	Approval required for certain antibiotics	
		Review of all positive blood cultures	

EHR, electronic health record; ID, infectious disease; STRAMA, Swedish strategic programme against antibiotic resistance; SWAB, Dutch working party on antibiotic policy.

### Study design

We plan to conduct an international, multicentre, stepped-wedge cluster randomised trial to assess whether making a smartphone app for AMS (Spectrum) can improve the appropriateness of antimicrobial prescribing in hospitalised patients. Table 2 illustrates the study question according to the Population, Intervention, Comparator, Outcome and Time (PICOT) framework.

**Table 2 T2:** PICOT of the study question

Population	Physicians involved in antimicrobial prescribing decisions for hospitalised adult patients in the participating centres
Intervention	Making a smartphone application with antimicrobial treatment recommendations available to physicians mentioned above
Comparator	Standard-of-care antimicrobial stewardship
Outcome	Appropriateness of empiric antimicrobial prescribing based on predefined criteria
Time	12 months consisting of a 6 months introduction period with 6 months follow-up to assess sustainability

In total, 36 medical and surgical entities (defined as wards (Sweden) or specialties (Switzerland, The Netherlands) will be included in the study using a stepwise design with six entities (two entities per participating hospital) 4-weekly at six introduction moments (figure 1). The primary outcome is appropriateness of empiric antimicrobial prescriptions assessed prior to implementation and up to 12 months after the intervention (after 6 months free use of the app). Empiric therapy is defined as^1^ treatment started based on clinical evaluation before culture results are known,^2^ the duration of treatment is longer than 24 hours (from the moment of prescription) and^3^ the treatment is not specifically recorded as prophylactic. Initial targeted therapy for which there is a local guideline available (eg, *Clostridium difficile*) may be assessed for appropriateness.

**Figure 1 F1:**
[figure not shown]
Study design. In all time periods (total of 7) there is an uptake period of 2 days and a measure period of 26 days. During the baseline period only a measure period of 2 weeks will be performed.

The entities will be randomised as to the time period of making the app available (see the Intervention section). The order of implementation will be determined by a computer-generated list of random numbers programmed by a statistician otherwise not involved in the trial and AMS activities. Randomisation will be stratified by the type of specialty (medicine, surgery, etc). After a baseline period of 2-week measurements, six periods of 4 weeks will follow in which the intervention is introduced in six entities (in three hospitals) until all entities have implemented the intervention. We plan to include 36 entities in total (see sample size calculation below) during the six introduction moments and at the end of the inclusion time we will allow the use of the app by everyone, also wards/specialties not included in the study. In this way, the trend in appropriate antimicrobial use can be monitored per ward/specialty and the decrease of antimicrobial use and appropriateness of empirical antimicrobial therapy can be followed during the stepwise implementation.^12^ At 12 months (after 6 months free use of the app) we will have a 2-week measurement period to evaluate the sustainability of the intervention. The study will start between February 2020 and June 2020, and end 12 months later.

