**Figure 3 F3:**
[figure not shown]
Interface of the AB-assistant app. On the left the Home screen is shown. In the middle checkboxes are shown to guide the user to the correct therapy for Meningitis. The right screen shows details about Amoxicillin-Clavulanate regarding dosing and general spectrum of activity.

For the purpose of this study the app and the content management system were extended to also support languages other than English (French, Dutch and Swedish) and will be used for prescribing guidelines, pathogens, antimicrobial drugs and antibiograms. App content such as local guidelines, information regarding antimicrobial drugs, and micro-organisms of each hospital was entered by investigators of the Dutch, Swiss and Swedish hospitals (RH, GC, BH and [name]). App content is identical to content of the local guidelines if these are published on a website. Minor discrepancies may occur if the local guidelines are published in a digital document (ie, PDF) or on paper. The app can be more up to date in those cases.

The allocation of the timing to introduce the app will be concealed to the participating cluster up until 2 weeks before initiating use of the intervention. At the start of the intervention physicians on the intervention ward(s) will be informed about the function and content of the app. During the trial, only physicians on the intervention wards will be whitelisted to be able to use the app. Access to the app will be centrally withdrawn if a physician leaves the intervention ward (eg, to work on a different (ie, non-intervention) ward). The conventional route of guidelines (eg, portable document formats (PDF), website or printed booklet) will still be available at all times. Physicians can freely choose between the app and the conventional route. Physicians on control wards will only be able to access the guidelines using the conventional route.

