## Statistical methods

Baseline characteristics of patients (eg, gender, age, allergies and comorbidities), use of antimicrobial drugs, appropriate antimicrobial therapy and other outcome parameters will be described by entity.

To mitigate possible differences in time trends and baseline characteristics at patient and centre level, primary analysis will be by centre and effect estimates will be combined over centres using meta-analytic methods. These primary analyses will employ multivariable multilevel logistic models with time periods as fixed effects to adjust for time trend and treatment as fixed effect to estimate the OR of treatment. Entities (ward/specialty) will be included as a random effect to account for the correlation of patients within entities, assuming this correlation is independent of time period of including the patient. Moreover, covariates will be included to adjust for age, gender, hospital and specialty (medical, surgical). Similar models but using (generalised) linear multilevel models will be used for continuous outcomes or incidence/rate outcomes.

Sensitivity analyses may include the following: adjusting for additional confounders if imbalance at baseline is present; investigating deviations from the assumption that the correlation of patients within entities is independent of time period of including the patient; estimating differences in percentage (instead of odds ratios) using a (generalised) linear multilevel models with identity link and binomial error distribution and incorporating the three centres in one model.

Subgroup analysis for specialty and other factors as appropriate will be conducted.

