### Sample size

By including 24 entities (wards/specialties) with seven measurement periods (including one baseline period) in which the primary outcome (appropriate empiric antimicrobial drug use) will be measured in 15 participating patients per entity per time period and an assumed intra-entity correlation coefficient of 0.1, the study has a power of 81% to detect an absolute improvement in appropriate antimicrobial use by 10 percentage points from of 60% to 70%.^16^ To account for potential drop-outs or a lower inclusion rate, we aim to include 36 clusters in the three participating hospitals.

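### The primary model's single treatment term assumes the full app effect from day 3 and a constant effect afterwards; if either fails, the estimate can sit well below or above the average effect

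*Protocol article*

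**What the plan says.** All references are to the protocol article.

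- **Transition window** (Study design, Figure 1 legend): "In all time periods (total of 7) there is an uptake period of 2 days and a measure period of 26 days". The legend then exempts the 2-week baseline. In each 4-week period, measurement therefore starts on day 3.
- **Primary model** (Statistical methods): a multilevel logistic model with "time periods as fixed effects to adjust for time trend and treatment as fixed effect to estimate the OR of treatment", plus a random entity intercept. It is fitted by centre and the estimates are then combined. There is one odds ratio and no term for time since introduction.
- **Sensitivity analyses** (Statistical methods): an open list that names extra confounders, the within-entity correlation over time, risk differences and one model for all centres. None of these lets the effect vary with time since introduction.
- **Layout** (Study design): "six entities (two entities per participating hospital) 4-weekly at six introduction moments", and "After a baseline period of 2-week measurements, six periods of 4 weeks will follow in which the intervention is introduced in six entities".
- **Use of the app** (Intervention): "Physicians can freely choose between the app and the conventional route". The Uptake analysis section tracks users and sessions monthly, and Study design adds a measurement at 12 months to look at sustainability.

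**The concern.** A single 0/1 term is correct if the effect arrives at once and stays level. If it does not, one would hope the term still reports some reasonable average over exposure time. In a stepped-wedge layout with fixed period effects it does not. The comparison leans on entities that have just crossed over, and long-exposed cells partly act as controls for later crossers.

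An effect that builds up is therefore pulled towards zero, and one that fades can be overstated. An app that works once adopted could be reported as doing little. An app whose benefit fades could be reported as fully effective.

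**Working it through.** **Inputs.** From Sample size: "By including 24 entities (wards/specialties) with seven measurement periods (including one baseline period"; the outcome "will be measured in 15 participating patients per entity per time period and an assumed intra-entity correlation coefficient of 0.1"; 60% against 70%; and "To account for potential drop-outs or a lower inclusion rate, we aim to include 36 clusters in the three participating hospitals". From Study design: 6 sequences with equal numbers of entities. My assumptions: two-sided alpha 0.05 (not stated), a linear scale with total variance 0.65 × 0.35 = 0.2275, and 15 patients in every cell including baseline.

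**Method.** For each entity, V has 0.1 × 0.2275 = 0.02275 in every cell, plus 0.9 × 0.2275 / 15 = 0.01365 on the diagonal. D holds seven period indicators and the 0/1 treatment column. The generalised least squares estimate is the last element of (ΣD′V⁻¹D)⁻¹ ΣD′V⁻¹Y.

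**The plan's own figure.** With 24 entities the SE is 0.0311, so power is Φ(0.10/0.0311 − 1.96) = Φ(1.26) = 0.896. The article states 81%. About 81% appears if the cluster autocorrelation (CAC) is 0.8. The stated figure is on the cautious side, and the gap does not affect this point. With 36 entities the SE is 0.0254 and power is 97.6%.

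**Weights.** Put a mean of 1 in exposure month j (a 4-week period) and 0 elsewhere; the expected treatment coefficient is the weight of that month.

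| Exposure month | 1 | 2 | 3 | 4 | 5 | 6 |
|---|---|---|---|---|---|---|
| Weight | 0.708 | 0.379 | 0.134 | -0.026 | -0.102 | -0.093 |
| Exposed cells (of 21) | 6 | 5 | 4 | 3 | 2 | 1 |

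The weights sum to 1. They depend on the layout, the ICC and the cell size, but not on the total variance. Each centre has the same layout with two entities per step, so analysis by centre gives the same weights.

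**Delayed effect.** Let the effect be 10 points from month 2 and a fraction f of that in month 1. The expected estimate is 10 × [1 − 0.708 × (1 − f)], and power with 36 entities is Φ(estimate/2.54 − 1.96).

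| f | Expected estimate (points) | Average over exposed cells | Equal-weight average over months | Power, 36 entities |
|---|---|---|---|---|
| 0% | 2.9 | 7.1 | 8.3 | 21% |
| 25% | 4.7 | 7.9 | 8.8 | 46% |
| 50% | 6.5 | 8.6 | 9.2 | 72% |
| 75% | 8.2 | 9.3 | 9.6 | 90% |
| 100% | 10.0 | 10.0 | 10.0 | 97.6% |

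For f = 0 the averages are (15 × 10)/21 = 7.1 and 50/6 = 8.3.

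**Waning effect (illustration).** With 10, 7.5, 5, 2.5, 0 and 0 points, the estimate is 7.08 + 2.84 + 0.67 − 0.07 = 10.5. The averages are 125/21 = 6.0 over exposed cells and 25/6 = 4.2 over months.

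**Robustness of the f = 0 case.** The estimate is 3.3 points at ICC 0.05, 2.7 at ICC 0.2, 3.1 at CAC 0.8, 2.6 with a half-size baseline, and 3.4 if the 12-month measurement were put into the model. A random-intercept logistic model fitted to simulated data gave an OR of about 1.16 against a true 1.61, or about 3.2 points.

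**The case against.** **The lag is not in the documents.** This stands. The article gives no uptake curve, and the 2.9-point case needs no effect at all for the whole first period. Uptake that rises within that period lies nearer the 50% or 75% rows. A reader might infer that the trial is heading for an estimate of 3 points; the documents do not support that. The range of about 3 to 8 points is what can be said.

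**Voluntary use and impediments to uptake do not show a delay.** This also stands. The Evaluation of use section concerns obstacles to uptake, not its timing. Stable partial uptake gives a constant, diluted effect, which the 0/1 term estimates properly. These features, with the sustainability question, show only that constancy is not assured.

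**Other parts of the plan might reveal a changing effect.** This stands in part. The ward-level trend, the link between app use and prescribing, and the 12-month measurement may hint at it. It would be too strong to say that nothing could show it. None of them qualifies the primary odds ratio, though, and at 12 months no unexposed entity remains for comparison.

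**This is the standard stepped-wedge model, the sensitivity list is open, and an analysis plan may add more.** Fair. The model is not an error, and the absence of detail is not the point. The point is what the stated primary model estimates in this stated layout when the effect is not constant.

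**Conclusion.** The point holds as a worthwhile improvement. The primary term puts 71% of its weight on the first exposure month and negative weight on months 4 to 6, so it is not an average over exposure. If the first month carries 0% to 75% of a later 10-point effect, the expected estimate is about 2.9 to 8.2 points and power with 36 entities is 21% to 90%. A fading effect can be overstated, by the illustration at 10.5 points against an average of 4.2 to 6.0.

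This rests on ICC 0.1, equal cells of 15, a linear approximation that the logistic check supports, and an assumed effect pattern. It does not show that a lag will occur or that the primary model should be replaced. If the effect is immediate and level, the planned estimate is right.

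**What to change.** Keep the 0/1 model as primary. Add to the sensitivity analyses under Statistical methods a pre-specified model with two treatment terms, one for the first 4-week exposure period and one for later exposure, reported beside the primary result. State that a null 0/1 estimate will not be read as no effect if the later-exposure term differs from it. A full exposure-time model, averaged over months, can be supportive.

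The change is analysis text only, because introduction dates are known. The price is precision:

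| Term | SE, 36 entities | Power for 10 points, 36 entities | Same at CAC 0.8 | 24 entities |
|---|---|---|---|---|
| Primary 0/1 term | 0.025 | 97.6% | 93% | 90% |
| Later-exposure term | 0.032 | 89% | 80% | 73% |
| Full exposure-time average | 0.039 | 72% | 63% | 55% |

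The two-term model removes the bias when only the first period differs. With a longer build-up or a fading effect, its later term is still a weighted mix, which is the reason to keep the full model as support despite its cost.

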### Justification of the stepped-wedge cluster randomised study design

The stepped-wedge cluster randomised design was chosen after considering several advantages and disadvantages of randomisation at the patient, physician, specialty and ward level. Patients are the ‘classic unit’ of randomisation and outcomes are often assessed at the patient level. However, there is a large risk of contamination of the intervention since one patient is often taken care of by many different physicians (see figure 2). Furthermore, the study intervention targets physicians and not patients, therefore precluding randomisation at the patient level as an option. Randomisation at the physician-level is, however, equally problematic since prescribing decisions in hospitals are often made by teams of physicians, making it difficult to assign a decision to a specific individual physician and introducing the risk of contamination between physicians within a team. We therefore decided to use the wards/specialty as entity of randomisation since it minimises the risk of contamination and reflects ‘real-life’ AMS in hospitals where interventions are usually implemented at a ward/specialty level.

